## **2. Objective and Outcomes**

### **2.1. Objective**

To evaluate the efficacy and safety of Y-2 Sublingual Tablets in the treatment of acute ischemic stroke.

### **2.2. Outcomes**

#### **2.2.1. Primary efficacy outcomes**

- The proportion of subjects with mRS score  $\leq 1$  on Day 90 after randomization.

**2.2.2. Secondary efficacy outcomes**

- mRS score on Day 90;
- The proportion of subjects with mRS score  $\leq 2$  on Day 9;
- Change in NIHSS score from baseline to Day 14;
- The proportion of subjects with NIHSS score of 0-1 on Day 14, Day 30, and Day 90 after randomization.

**2.2.3. Safety outcomes**

- Incidence of adverse events (AEs) in each group;
- Incidence of treatment-related adverse events (TEAEs) in each group;
- Changes in vital signs and laboratory data in each group before and after treatment.

**2.3. Main estimated target**

The main clinical concerns of this study: Based on treatment policy strategy, the efficacy of Y-2 Sublingual Tablets versus placebo in patients with acute ischemic stroke was assessed by the proportion of participants with an mRS score  $\leq 1$  at Day 90 after treatment, regardless of whether the participants had delayed or discontinued the administration, or used protocol-allowed concomitant medications (as specified in Section 5.8.1) due to adverse events.

The main estimated target consists of the following attributes:

- Population: adult patients with acute ischemic stroke. The study population in this trial is determined by the inclusion and exclusion criteria defined in Section 4;
- Treatment: Y-2 Sublingual Tablets 36 mg (containing 30 mg of edaravone and 6 mg of dexborneol) or Y-2 placebo control (containing 60  $\mu$ g of dexborneol to simulate the cool taste of sublingual administration of the investigational product) BID for 14 consecutive days, 28 times in total;
- Endpoint: treatment compliance status derived from the mRS score at Day 90 after treatment (compliance: mRS score  $\leq 1$ );
- Handling of other concomitant events:
  - Use of concomitant medications/therapies during the treatment period but continued with investigational product treatment and follow-up after

investigator assessment; or delay, interruption of administration, or discontinuation of the treatment due to AEs, but no early withdrawal from the study; or mRS scores at required time points could only be obtained through remote visit due to the impact of COVID-19: Use of treatment policy strategy (regardless of the occurrence of such events);

- No mRS score after initiation of the treatment for any reason; or early discontinuation of treatment or withdrawal from the study due to death; or early withdrawal from protocol-specified follow-up due to AEs: use of a composite strategy (occurrence of such events was counted as a substandard mRS score);
- Early discontinuation of the treatment or withdrawal from the study for reasons other than those mentioned above: use of the while-on-treatment strategy (i.e., mRS compliance status was evaluated based on the mRS score closest to the withdrawal from the study).
- Population-level summary: The proportion of patients whose mRS score  $\leq 1$  in the Y-2 Sublingual Tablets treatment group and the placebo treatment group was summarized based on the mRS score at Day 90 after the treatment for 14 days in line with the established treatment protocol, and the rate difference between the two groups was calculated.

### **3. Study design**

#### **3.1. General design**

It is designed as a multicenter, randomized, double-blind, parallel, and placebo-controlled trial.

The trial is divided into three phases: screening/baseline period, treatment period, and follow-up period.

**Screening/baseline period:** The subjects enter the screening/baseline period after signing the informed consent form.

Prior to random grouping, at least the information and examinations involved in the inclusion and exclusion criteria should be completed and confirmed by the authorized

investigator. The rest of the baseline tests only require the collection of test samples prior to the first dose.

If the subject has completed the examinations required by the protocol within 24 hours after this onset and admission, and investigators consider it sufficient to support the diagnosis of the subject's condition, the examination may not be conducted again, as repeated examinations in a short time may impact the health of the subject or seriously affect the treatment time of the subject. The subject can directly reimburse the corresponding expenses to the Sponsor with the examination bills and details, and the specific expenses will be reimbursed according to the policies of the site.

**Treatment period:** Eligible subjects are randomly assigned to receive Y-2 Sublingual Tablets or Y-2 placebo for 14 consecutive days, during which the relevant tests as required by the protocol are performed and safety is assessed.

**Follow-up period:** Subjects after the treatment are followed up until Day 90 of treatment. Stroke Scale is used for scoring on Day 14, Day 30, and Day 90 after the first dose of the investigational product, and adverse events are recorded during follow-up periods to further assess safety.

The detailed study process and observation items are shown in the flow chart.

### **3.2. Sample size**

It is preliminarily planned to enroll 914 subjects in this trial, Y-2 Sublingual Tablets group: Y-2 placebo control group = 1:1, Y-2 Sublingual Tablets group: 457 subjects, and placebo control group: 457 subjects. An interim analysis is scheduled to be performed after approximately 50% of subjects complete the visit on Day 90. The purpose of interim analysis is to reestimate the sample size based on primary efficacy indexes. It is conducted by the Independent Data Monitoring Committee (IDMC) and whether the sample size should be increased or remain unchanged is recommended according to the regulations of the IDMC. The sample size may be increased to 1.5 times the scheduled sample size at most, and won't be reduced.

### 3.3. Scientific basis for trial design

Since the 20th century, except edaravone, almost all neuroprotective agents targeting a single target or a single pathway have been clinically proven ineffective. Studies have confirmed that acute ischemia leads to abnormal cellular energy metabolism and a series of ischemic cascade responses. In the very early stage after cerebral ischemia, local neuronal protein synthesis stops, membrane ion transport stops, neuronal depolarization occurs, and calcium influx leads to the release of a large amount of excitatory amino acid-glutamate. Cellular damage increases as such release aggravates calcium influx and neuronal depolarization; A large number of calcium ions enter the cell through the damage of NMDA/AMPA receptors, metabolic glutamate receptors and voltage-dependent calcium channels, and activate proteases, lipases, various kinases, nucleases and nitric oxide (NO) synthases, resulting in dysfunction of cell stability and destruction of cytoskeleton, mitochondria and cell membrane; Subsequently, the formation of free radicals and NO synthesis exacerbate further neuronal damage; In addition, the inflammatory reaction, leukocyte adhesion and infiltration, and cytokine action accompanying reperfusion will further enhance the destruction of nerve cells after ischemia and aggravate microcirculatory disorders. In the end, the activation of apoptotic genes leads to programmed cell death, resulting in the fusion of the ischemic penumbra with necrosis. It is analyzed that the clinical failure of neuroprotective drugs is largely related to the inconsistency between the action mode of neuroprotective agents and the mechanism of ischemic brain injury. Due to the complexity of ischemic mechanism, the single action mode of a single drug cannot fully protect other mechanisms of ischemic brain injury, such as apoptosis, glial cells, inflammation and intracellular mechanisms; Early and multipathway (cocktail) therapy may be a reasonable direction for neuroprotective therapy for the cascade reaction mechanism of the ischemic injury. For example, experiments with a combination use of excitatory amino acid antagonists and free radical scavengers have shown to be more effective than their respective use. Therefore, the development of multi-target or multi-pathway compound preparations is a hot trend in the international research on effective treatment of stroke.

Ischemic cerebrovascular diseases are acute and need to be relieved quickly, so injection

is the first choice for emergency treatment. However, intramuscular injection or intravenous injection can cause pain and irritation at the injection site, so it requires professional medical personnel to operate and inject products. Due to certain medical restrictions in application, it is difficult to apply to patients with out-of-hospital onset. Therefore, there is also an urgent clinical need for effective neuroprotective agents that are administered in different non-injectable modes to benefit more patients. Sublingual preparations are absorbed directly from the sublingual mucosa. The sublingual mucosa has a large surface area and strong osmotic capacity. In addition, there are numerous capillaries under the mucosa that are pooled into the internal jugular vein and directly enter the blood circulation through the superior vena cava. Therefore, drugs can be quickly absorbed after administration, with rapid onset of action, accurate quantification, and convenient use, thus avoiding the first pass effect of oral drugs. Compared with injections, sublingual preparations, especially sublingual tablets, can greatly improve the convenience of medication and the compliance of clinical patients for cerebrovascular diseases. At the same time, many stroke patients have dysphagia, so sublingual tablets are more advantageous than oral preparations.

The main components of Y-2 Sublingual Tablets are edaravone (30mg) and dexborneol (6mg). Edaravone injection, as a neuroprotective agent, is one of the drugs recommended in the Chinese Guidelines for Diagnosis and Treatment of Acute Ischemic Stroke [5] for the treatment of acute ischemic cerebral infarction. Its clinical dose is 30 mg. The phase I clinical PK study of Y-2 Sublingual Tablets has demonstrated that the exposure of edaravone in human body after the administration of 1 tablet of Y-2 Sublingual Tablets is similar to that of intravenous drip of edaravone 30 mg solution, so the recommended dose of Y-2 Sublingual Tablets is 1 tablet.

### **3.4. Hospitalization time**

The trial has no mandatory requirement for the hospitalization time of subjects. The hospitalization time is subject to the treatment time required for the condition of subjects during the baseline period.

### **3.5. Definition of end of study**

- Determine the final sample size according to the interim results, complete the

enrollment and visit of all sample sizes, and end the trial;

- The Sponsor and investigator jointly decide to discontinue the trial based on the risk and benefit of patients.

#### **4. Population**

##### **4.1. Inclusion criteria**

Those who meet all the following requirements:

- Age  $\geq 18$  years old and  $\leq 80$  years old, regardless of gender;
- After the onset of the disease, the National Institutes of Stroke Scale score:  $6 \leq \text{NIHSS} \leq 20$ , and the sum of the fifth upper limb score and the sixth lower limb score was  $\geq 2$ ;
- The onset time is within 48 hours (including 48 hours);
- Patients diagnosed as ischemic stroke according to "key points for diagnosis of all kinds of major cerebrovascular diseases in China 2019", with good prognosis after the first attack or the last attack (MRS score  $\leq 1$  before this attack);
- The informed consent approved by the ethics committee was voluntarily signed by the patient or his legal representative.

##### **4.2. Exclusion criteria**

Those who meet any of the following items:

- Intracranial hemorrhagic diseases seen in head imaging: hemorrhagic stroke, epidural hematoma, intracranial hematoma, intraventricular hemorrhage, subarachnoid hemorrhage, etc; If it is only oozing blood, the researcher can judge whether it is suitable for inclusion;
- Severe disturbance of consciousness: the item score of La consciousness level of NIHSS was more than 1;
- Transient ischemic attack (TIA);
- Systolic blood pressure was still higher than 220mmhg or diastolic blood pressure was higher than 120mmhg after blood pressure control;
- Patients with severe mental disorders and dementia;

- Severe active liver diseases have been diagnosed, such as acute hepatitis, chronic active hepatitis, cirrhosis, etc; Or ALT or AST  $> 2.0 \times \text{ULN}$ ;
- Severe active kidney disease and renal insufficiency have been diagnosed; Or serum creatinine  $> 1.5 \times \text{ULN}$ ;
- After the onset of the disease, the drugs with neuroprotective effect in the manual have been used;
- Embolectomy or interventional therapy has been used or planned after the onset of the disease;
- Complicated with malignant tumor or undergoing anti-tumor treatment; For the subjects diagnosed with malignant tumor after enrollment, whether to continue to participate in the study can be judged by the researcher and the willingness of the subjects;
- Suffering from severe systemic diseases, the estimated survival time is less than 90 days;
- Allergic to d-borneol or edaravone or excipients;
- Patients during pregnancy, lactation, and planned pregnancy;
- Major operation history within 4 weeks before enrollment;
- Have participated in other clinical studies or are participating in other clinical studies within 30 days before randomization;
- The researcher thinks that it is not suitable to participate in this clinical study.

If a subject is found to have violated the inclusion criteria or met the exclusion criteria after enrollment, investigators may judge whether the subject is suitable to continue the study based on the risks and benefits.

#### **4.3. Definition of onset time**

The onset time of stroke is defined as the time when the patient's symptoms start. If the onset occurs during sleep, the onset time is the time when the patient last acted normal.

The 48 hours specified in the protocol are the time from onset to the first administration of the investigational product.

## **5. Study treatment**

### **5.1. Study drug**

#### **Investigational product**

Y-2 Sublingual Tablets, each contains 30 mg of edaravone and 6 mg of dexborneol. Batch No.: Q0120006; Expiry date: June 16, 2022.

#### **Control product**

Placebo control was used in this study.

Y-2 is a Class I new drug, and there is no similar drug recognized and validated to be effective, so placebo is used as the control.

Y-2 placebo contains 60 µg of dexborneol to simulate the cool taste of sublingual administration of Y-2 Sublingual Tablets. This dose is verified to have no efficacy by animal experiments, and its composition of excipients is consistent with that of the Y-2 Sublingual Tablets. Batch No.: Q0120001; Expiry date: June 13, 2022.

Multiple batches of drugs may need to be prepared in this trial study, and relevant materials will be submitted for filing before the adoption of new drugs.

#### **Storage condition**

This product should be stored in a sealed and cool place (not more than 20°C), with a tentative shelf life of 2 years. In the influencing factor test, it is stable at a high temperature of 40°C with packaging for 1 month. Therefore, the drug needs to be stored in a cool place (not more than 20°C) for long-term storage, and can be exposed to the environment not more than 40°C for a short time (1 month).

### **5.2. Management of study drug**

#### **5.2.1. Packaging and labeling of study drug**

The investigational product and the control product are identical in color and shape. In order to keep it blind, the packaging of the two groups of drugs are identical, the package batch number is uniformly marked, and the shortest shelf life of the two drugs is selected as the shelf life.

Each randomized subject will be assigned a large box of drugs with the corresponding drug number, which contains 30 small boxes (including 2 small boxes of backup drugs); each small box contains 1 tablet of drug for one use.

The specific drug filling specifications and quantity are shown in Table 5.2- 1:

**Table 5.2- 1 Drug Filling Specification**

| Group    | Number of large boxes | Number of small boxes | Drug in each small box Composition |
|-----------------|------------------------------|------------------------------|-------------------------------------------|
| Treatment group | 1                            | 30                           | 1 tablet                                  |
| Control group   | 1                            | 30                           | 1 tablet                                  |

The contents of the package label of this clinical investigational product are as follows:

**Label of large box package**

**Clinical investigational product of Y-2 Sublingual Tablets for the treatment of acute ischemic stroke**

**Drug No.:** \_\_\_\_\_

**This product is for clinical trials only**

[Packaging] A total of 30 small boxes with 1 tablet in each small box.

[Strength] 30 mg of edaravone and 6 mg of dexborneol; or 60 µg of dexborneol

[Administration and dosage] Take 1 tablet of the drug sublingually each time.

Place the drug at the edge of the lingual frenulum, and keep it until there is no obvious foreign body sensation. Avoid chewing or swallowing undisintegrated drugs directly during administration.

[Storage] Sealed and stored in a cool place (not more than 20°C)

[Manufacturer] 2Y-Biopharma Ltd.

[Product batch No.] Q0120001\Q0120006

[Expiration date] June 13, 2022

[Note] **The remaining unused drugs should be recycled to the Sponsor and kept away from children.**

#### **Label of small box package**

**Clinical investigational product of Y-2 Sublingual Tablets for the treatment of  
acute ischemic stroke**

**Drug No.: \_\_\_\_\_**

**This product is for clinical trials only**

[Packaging] 1 tablet in each box.

[Strength] 30 mg of edaravone and 6 mg of dexborneol; or 60 µg of dexborneol

[Storage] Sealed and stored in a cool place (not more than 20°C)

[Manufacturer] 2Y-Biopharma Ltd.

[Product batch No.] Q0120001\Q0120006

[Expiration date] June 13, 2022

[Note] **The remaining unused drugs should be recycled to the Sponsor and kept away from children.**

Note: To keep it blind, the product batch number on the label includes the batch number of the investigational product and the control product, and the shortest shelf life of the two drugs is selected as the shelf life.

#### **5.2.2. Receipt and storage of study drug**

All study drugs in this study are supplied by the Sponsor in a unified manner. the sites

should assign special personnel to receive and store the study drugs. It is the responsibility of the site to receive and store the study drugs in accordance with applicable regulatory requirements and the Sponsor's designated requirements.

All study drugs should be stored in a safe area until dispensed to the subjects, and are accessible only to those involved in the clinical study. The study drug management personnel should fully supervise the storage environment, and keep relevant temperature logs as source documents. All study drugs must be used in this study and cannot be used for other purposes.

The investigators should ensure that all study drugs are used as specified in this protocol.

#### **5.2.3. Distribution, recovery, and destruction of study drug**

In order to strictly manage and use the study drugs, the sites should have dedicated personnel responsible for the management of study drugs, including distribution, recovery, and destruction, and ensuring that all documents related to the study drugs generated during the study are recorded in a timely and accurate manner.

Each site should assign special personnel to manage and distribute study drugs. Drug management personnel should distribute the study drugs to subjects according to the requirements of the clinical trial protocol, and timely record the distribution and recovery of each study drug in a special record sheet.

Study drugs may not be used for any purpose other than that described in the clinical trial protocol. Investigators should ensure that all investigational drugs are only used for subjects involved in the clinical trial with the administration and dosage specified in the clinical trial protocol. Study drugs may not be transferred to any non-clinical trial subjects.

Monitors are responsible for overseeing the management process of study drugs.

All unused study drugs should be recovered and destroyed by the Sponsor. The Sponsor will provide destruction records.

#### **5.3. Randomization and blinding**

It is designed as a multicenter, randomized, double-blind, parallel, and placebo-controlled trial. Subjects are randomized in a 1:1 ratio. Random number table is generated by simulation using standardized software.

The trial adopts a randomized method of centralized competitive enrollment. Each subject will be assigned a "screening number" after signing the informed consent form and before conducting study-related examinations. The screening numbers of subjects should not be reused.

After qualified subjects are selected after the screening, investigators or their designated personnel obtain the randomization number and corresponding drug number through the randomization system, and distribute corresponding study drugs according to the randomization number and drug number.

Stratified randomization factors include:

Onset time:  $\leq 24$  hours VS  $> 24$  hours;

Sites.

The color, description, and packaging (including batch number and expiration date) of the investigational product (Y-2 Sublingual Tablets) and placebo control (Y-2 placebo) are the same. The blinding process is completed by statisticians unrelated to this clinical trial. After the blinding, blind codes will be sealed in duplicate and stored in the leading unit and the Sponsor respectively.

## **5.4. Unblinding**

### **5.4.1. Common unblinding regulations**

The one-time unblinding method is adopted in this trial. After blind verification, the data will be locked and unblinded, and the corresponding group of each subject will be defined.

For interim analysis, the unblinded data will be centrally reviewed by IDMC members according to IDMC regulations. Statistical analysis of the data will be completed by third-party unblinded statisticians independent of the Sponsor, so as to keep blinding during the trial.

### **5.4.2. Emergency unblinding**

Emergency unblinding is allowed only in the following circumstances: in case of a serious adverse event suspected to be related to the investigational product, the principal investigator of the site should report to the Sponsor to decide whether to initiate the emergency unblinding procedure. Once the emergency unblinding is conducted, the case is

considered dropped out. If the emergency unblinding happens during the treatment period, the medication should be stopped.

This double-blind trial will be invalid if all blind codes are disclosed or the emergency unblinding rate exceeds 20% during the study.

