### **7.3.7. Serious adverse event reporting to the Sponsor**

The investigator or designee must complete the rapid SAE reporting within 24 hours of being informed of the occurrence of SAE in the subject, which should include as detailed and useful content as possible. Even if not all the information of the SAE is available at that time, it still needs to be reported within 24 hours. The SAE report should be updated by the investigator within 24 hours after additional relevant information is available.

The investigator or designee will fill in the relevant information using the Jiangsu *Simcere Serious Adverse Event (SAE) Report Form*, print and then sign the date and name, and send the scanned copy to the Sponsor by email ([contact]) within 24 hours.

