### **7.3.8. Pregnancy**

All subjects should use reliable contraceptives for 30 days from signing the informed consent form to the last dose to avoid pregnancy of themselves or their female partners. If any pregnancy (including pregnancy confirmed after 90 days) occurs in the subject (or male subject's female partner) within 90 days from the time when the subject receives at least one dose of the investigational product to the last dose, the investigator should examine the safety of the subject and the fetus and take appropriate actions upon discovery; record the pregnancy information in the pregnancy report form and report to the Sponsor within 24 hours after obtaining the information.

All pregnancies should be tracked to outcome until the infant is full term (usually 6 to 8 weeks after the expected date of delivery) or early termination of pregnancy (including spontaneous or selective abortion).

Although pregnancy is not considered an AE or SAE, pregnancy complication or selective termination of pregnancy should be reported as an AE/SAE. Abnormal pregnancy outcomes (e.g., spontaneous abortion, fetal death, stillbirth, congenital anomalies, ectopic pregnancy) are considered SAEs and reported as SAEs (*Simcere Pregnancy Report Form* and *Simcere Serious Adverse Event (SAE) Report Form* are required to be completed at the same time).

In principle, any female subject who becomes pregnant during the study period should immediately discontinue the investigational product.

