#### **9.6. Protocol deviation**

In the absence of pre-review and consent granted by the Sponsor or the Sponsor's agent, the investigator shall not violate the protocol unless it is necessary to eliminate immediate harm to subjects in the study under the premise of following the EC and local regulations. When a violation resulting from protocol implementation is deemed necessary for an individual subject, the investigator must contact the Sponsor as soon as possible to obtain the Sponsor's review and confirm the impact of the violation on subjects and/or the study. Any major protocol violation that affects the subject's eligibility and/or safety is subject to the review and/or approval by EC and regulatory authorities; It should be implemented before the protocol implementation if feasible.

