## 2.6 Randomization and Blinding

All eligible subjects will be randomly assigned to the investigational or control group according to the ratio of 1:1. The random number table is generated by the standardized software. The detailed parameter settings are set by the randomization plan.

In this trial, a centralized competitive enrollment randomization method will be used, and subjects will be assigned a "screening number" after signing the informed consent form and before performing study-related tests. Subject screening numbers must not be reused.

After the subjects passed screening, the investigator or designee obtained the information of randomization number and corresponding drug number through the randomization system, and distributed the corresponding study drugs according to the randomization number and drug number.

Randomization will be stratified by:

- Onset time:  $\leq 24$  hours vs  $> 24$  hours;
- Investigational site.

The color, description, and packaging (including batch number and shelf life) of the investigational drug (Y-2 sublingual tablet) and placebo control drug (Y-2 sublingual tablet placebo) were identical. Blinding process was completed by statisticians unrelated to this clinical trial. After blinding, the blinding codes will be sealed in duplicate and stored in the leading site and the sponsor, respectively.

The trial was unblinded just once. After the last subject completes the 90-day follow-up in the whole trial, after blind verification, the data is locked and unblinding is performed, that is, the corresponding group of each subject is identified. For interim analysis, according to IDMC charter, unblinded data will be reviewed centrally by IDMC members and their statistical analysis will be performed by a third party unblinded statistician independent of the study project team to ensure blinding during the conduct of the trial.

When a serious adverse event suspected to be related to the investigational drug occurs during the trial, the principal investigator at the site should report to the sponsor to decide whether to initiate the emergency unblinding procedure. Once the blind was broken emergently, the case was treated as a dropout and medication was stopped if the blind was broken emergently during treatment.

This double-blind trial was invalidated if the total blind codes were leaked or emergency unblinding exceeded 20% during the study.

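### The emergency unblinding rule has a single trigger and runs through the Sponsor, which leaves the treating investigator no independent, timely route to a patient's allocation

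*Combined protocol and SAP*

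**What the plan says.** **Trigger.** Protocol 5.4.2 reads: "Emergency unblinding is allowed only in the following circumstances: in case of a serious adverse event suspected to be related to the investigational product". No other circumstance is listed. SAP 2.6 opens the same rule with "When a serious adverse event suspected to be related to the investigational drug occurs during the trial", which names the same event but does not make it exclusive.

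**Route.** Under protocol 5.4.2, "the principal investigator of the site should report to the Sponsor to decide whether to initiate the emergency unblinding procedure". SAP 2.6 says the same: "the principal investigator at the site should report to the sponsor to decide whether to initiate the emergency unblinding procedure".

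**Custody of the codes.** Protocol 5.3 states that "blind codes will be sealed in duplicate and stored in the leading unit and the Sponsor respectively", and SAP 2.6 repeats this. Sites use a randomisation system to obtain a randomisation number and a drug number. Neither document says whether that system can reveal an allocation.

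**Consequence.** Both documents treat an emergency-unblinded case as a dropout and stop the medication if the break happens during treatment. Both declare the double-blind trial invalid if emergency unblinding exceeds 20%.

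**General exception.** Protocol 9.6 says "the investigator shall not violate the protocol unless it is necessary to eliminate immediate harm to subjects in the study", which excuses prior Sponsor consent in that situation. Protocol 9.2.3 has a similar exception to prior ethics committee approval. Neither section mentions unblinding.

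**The concern.** Emergency unblinding exists so that the person caring for a patient can learn what was given when care depends on it. A procedure that serves this purpose needs a trigger tied to that need, a decision-maker who is at hand, and physical access to the code. Here the trigger is one category of event, the decision passes through a party away from the bedside, and the described codes are kept at two places.

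What is at stake is first a safety control that could be delayed or blocked when it is needed. There is also a statistical cost. Calling every unblinded case a dropout invites the loss of the Day 90 mRS in patients with suspected serious reactions, who are not a random subset. SAP 4.3.1 anticipates missing Day 90 scores after emergency unblinding and assigns them to an intercurrent-event strategy by the reason on the CRF. Withdrawal from follow-up for an adverse event then counts as failure, and withdrawal for other reasons uses the nearest mRS. An outcome that could have been observed is replaced by a rule.

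**Working it through.** This is a procedural point, so there is no plan figure to reproduce. The check sets the relevant sections side by side and asks four questions.

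| Question | Protocol | SAP | Result |
|---|---|---|---|
| What permits a code break? | 5.4.2: only an SAE suspected to be related | 2.6: same event, no 'only' | One trigger; the documents differ on whether it is exclusive |
| Who decides? | 5.4.2: the site principal investigator reports to the Sponsor for a decision | 2.6: same | Sponsor contact comes first |
| Where is the code? | 5.3: leading unit and Sponsor | 2.6: same | No site copy or site access described |
| How fast? | Not stated | Not stated | No limit on the decision |

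**Step 1, who decides.** The translated phrase can be read as the Sponsor deciding or as the investigator deciding after reporting. The first is the natural reading. The finding does not depend on it: under either, the Sponsor must be contacted first and no independent route is described.

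**Step 2, do the general exceptions fill the gap?** Protocol 9.6 could supply authority to depart from 5.4.2 when harm is immediate, and 9.2.3 does so with respect to ethics approval. But 5.4.2 uses 'only', so an investigator in an emergency faces two rules that disagree. Neither exception says how a code would be obtained. Even if authority is granted, access is not.

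**Step 3, who lacks described access?** The protocol synopsis plans about 40 centres. If the leading unit is itself one of them (an assumption), 40 − 1 = about 39 sites hold no described code set. The rule applies to every randomised patient, 914 as planned.

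**Step 4, does the 20% limit argue against wider access?** Taking randomised patients as the denominator (also an assumption), 0.20 × 914 = 182.8, so the limit is passed at 183 or more emergency code breaks. The documents give no expected number of emergencies, so this shows only where the limit lies.

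**Step 5, analysis status.** Protocol 8.2 and SAP section 3 put all randomised subjects in the full analysis set, so an unblinded patient is already in it. The dropout label in 5.4.2 and SAP 2.6 does not remove the patient, but it does nothing to secure the Day 90 score. It also sits awkwardly with the treatment policy strategy, under which patients who stop treatment because of an adverse event but remain in the study are assessed on their measured score.

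**The case against.** The strongest reply is that 9.6 already frees the investigator from prior Sponsor consent when harm is immediate, that treatment can be stopped under 5.7.1 without unblinding, and that a code-break function may be described in the randomisation plan or a system manual that is not in these documents. Each has force. Because of 9.6, a reader who infers that the investigator can never act without the Sponsor goes too far; the text supports only that no route is provided. Stopping the drug will be enough in many cases. An unseen system function would solve access, but 5.4.2 as written would still not allow its use outside the stated trigger and route.

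Several stronger readings are tempting and are not supported:

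- **A life-threatening event of unclear cause is excluded.** Such an event is an SAE, and the causality scale in 7.3.5 includes a 'possibly related' grade, so it can qualify as suspected.
- **Pregnancy or a child's accidental ingestion shows the rule failing.** Protocol 7.3.8 says a pregnancy is not an AE or SAE and that "the investigator should examine the safety of the subject and the fetus and take appropriate actions upon discovery", but it makes no step depend on the allocation. The child example rests on a label line, and 5.6 foresees no serious consequence of mistaken intake.
- **The SAE timeline proves delay.** The site "must complete the rapid SAE reporting within 24 hours of being informed of the occurrence of SAE in the subject". That is an outer limit on the site's report. It neither holds back an earlier call nor governs the Sponsor's reply.
- **The rule contradicts protocol 8.6.** That section protects interim-analysis information, not individual emergency codes.
- **The Sponsor learns individual allocations.** The text concerns whether to start the procedure and does not say who sees the code.

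**Conclusion.** The point holds as a defect in a stated rule rather than a mere lack of detail. Protocol 5.4.2 limits emergency unblinding to one trigger and puts the Sponsor in the path; SAP 2.6 repeats the path and drops the exclusivity; the described codes are away from most sites; no time limit is set; and the immediate-harm clauses conflict with 'only' without providing a code. The treating investigator is therefore given no independent, timely route to the allocation.

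The size cannot be put as a number of patients harmed or hours lost. The rule covers all 914 planned patients, but the frequency of emergencies in which care depends on the allocation, and the Sponsor's response time, are not in the documents. The conclusion assumes that no separate document grants sites direct access. If one does, the contradiction with 5.4.2 remains and the access gap closes. A change is warranted because it is cheap and concerns patient safety. Nothing here shows that any patient was in fact denied a code break.

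**What to change.** 1. **Amend protocol 5.4.2 and SAP 2.6 in identical terms.** The site investigator may break the blind for an individual patient, through the randomisation system already in use, when knowing the allocation is needed for that patient's safety. Prior Sponsor agreement is not required.
2. **Log and notify.** Record the reason and the time. Tell the Sponsor afterwards that a code was broken, without the allocation going to the project team.
3. **Reconcile with 9.2.3 and 9.6**, so that the unblinding rule and the immediate-harm clauses say the same thing.
4. **Replace the automatic dropout label.** State that an unblinded patient remains in follow-up and in the full analysis set, with the Day 90 mRS collected. Align SAP 4.3.1 so that its handling applies only where the score is truly missing.
5. **Reconcile the text on stopping medication** after a code break with the new rule. Which clinical rule should apply is for the sponsor and investigators to settle.

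The cost is wording in two documents, a code-break function in the randomisation system if none exists, and possibly a few more unblinded patients, each of them logged. The 20% limit can stay.

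The minutes of the third IDMC meeting record that all 914 patients have finished follow-up, so new wording helps only if this protocol is reused. For this trial, the sponsor can report how many unblinding requests were made, granted or refused, how long each took, who learned the allocation, and whether a Day 90 mRS was obtained.
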